### Intervention fidelity

To monitor intervention fidelity, each therapist will be required to maintain a detailed log of the type and frequency of interventions and an audit of detailed intervention plans describing each intervention undertaken, audit of care plans and a supervision log.

### Economic evaluation

Comprehensive data on health and social care service use and medications used by participants in the study will be collected using a tailored version of the CSRI. We will also collect data on staff inputs and support received by the study participants as part of the interventions.

Services and staff inputs will be costed as long-run marginal opportunity costs (LRMCs) using national figures. Where national figures are not available or not suitable, we will calculate best estimates of LRMC values from locally collected expenditure figures. Data on intervention costs and service costs will be examined alongside data on the main outcomes in a series of cost-effectiveness analyses. Each cost-effectiveness analysis will be conducted from the perspective of the NHS and social services.

Quality-adjusted life-year (QALY) gains generated from the DEMQOL will be used in turn in a series of cost-effectiveness analyses. The evaluation will include the plotting of cost effectiveness acceptability curves generated from bootstrap analyses. Sensitivity analyses will explore the impact of changes in the findings in key costs and outcome assumptions.

### Care home selection: inclusion and exclusion criteria

Care homes with a high proportion of residents thought to have dementia will be identified, screened and recruited to the study as described below.

An initial search for suitable care homes will be made using local care home directories (this will include care homes that are part of care home research networks). These care homes will be screened for the following inclusion/exclusion criteria.

Inclusion criteria:

• Care homes that identify themselves as catering for people with dementia within their literature

• Care homes that are able to demonstrate a minimum acceptable standard of care according to the Care Quality Commission (CQC)

Exclusion criteria:

• Less than 60% of the residents have dementia

• Care home is receiving special support from their local authority

• Care home has failed to meet the five CQC care home quality standards checks with more than one black mark (at least one standard in this area was not being met and improvements are required) or one red mark (at least one standard in this area was not being met and enforcement has been taken):

1. Standards of treating people with respect and involving them in their care

2. Standards of providing care, treatment and support which meets people’s needs

3. Standards of caring for people safely and protecting them from harm

4. Standards of staffing

5. Standards of management

The research teams in each study site will contact all care homes meeting the inclusion/exclusion criteria on the list by email, mail and/or phone call. The aims of this exercise will be to:

• Find out whether the care home might be interested in participating in the study; and

• Screen care homes further against secondary exclusion criteria to determine their suitability.

Secondary exclusion criteria:

• Insufficient staffing resource. Care home unable to provide care staff champions or staff able to act as informants for participant assessments

• Anticipated major change. Anticipated events or major changes anticipated to take place in the next 12 months, which might impact involvement in the research

• Involvement in other research. Care home involved in other research projects, which might affect their suitability to take part in this study or place too much burden on staff and residents

• Undergoing systematic programme of service improvement: Care home involved in a systematic programme of service improvement (such as intensive Dementia Care Mapping).

Once a care home meets the inclusion/exclusion criteria and the manager has given consent for the study to take place, the identifying, consenting and baseline assessments will commence. Once this process has been completed, the researcher will randomise the care home using NWORTH’s online randomisation system. Then the study site will initiate the main trial procedures at the care home.

Care home withdrawal from the study will be considered on an individual basis with the home in the event circumstances change following the consent procedures.

### Recruiting centres

Three recruiting hubs based in London and Buckinghamshire will each aim to recruit between 20 and 25 care homes.

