**Design:**

The trial will be a randomised controlled two-arm cluster single blind trial that will take place for nine months across 80 care homes in the United Kingdom.

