## Methods/design

### Overall design

The study design is a cluster randomised controlled, two-arm trial to be run in up to 80 care homes. It is estimated that each cluster will include a minimum of 12 participants. Each cluster in the optimised WHELD intervention arm will receive the intervention for nine months. Evaluations will be undertaken to understand the breadth of benefits conferred by the intervention to be assessed when used in comparison with the progress of the participants residing in the care homes allocated to the treatment as usual (TAU) trial arm.

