### Number of participants and power of the study

Up to 80 suitable care homes, or units within larger homes, will be identified, recruited and randomised, and the minimum target participant recruitment is 12 individuals with dementia per care home. Therefore, the target minimum sample size is 960, with a suggested upper recruitment limit of approximately 1,280 (that is, 16 individuals with dementia per care home). There will be no more than two units in any care home.

Baseline and follow-up data will be collected on all consented residents who meet the inclusion criteria at each participating care home. Taking into account the likely loss to follow up, it is estimated that, on average, 8 of the 12 will be followed up at nine months, giving a total sample size of 640. This trial is cluster randomised to take account of the fact that the participants live together in care homes. Re-analysis of data from previous studies suggests that intra-home correlation coefficients rarely exceed 0.05. As the ‘variance inflation factor’ (VIF) of this cluster randomised trial [1 + (8 - 1) × 0.05] = 1.35, the likely useable sample size of 640 participants will give 90% power using a significance level of 5% to detect a standardised effect size of 0.3 SDs, which is usually taken as the lowest threshold of a clinically meaningful benefit [13].

The observed SD for our population on DEMQOL taken from our pilot study is approximately 12. The standard error of measurement (SEM), derived by multiplying the SD of the sample by the square root of one minus its reliability coefficient, has been described as a useful statistic for assessing individual change on health-related QoL instruments [14]. Smith *et al.*[15] reported DEMQOL’s reliability coefficient as 0.82. Therefore, the SEM for this data is 12*sqrt (1-.82) = 5.1. This provides further support that we are measuring clinically meaningful change in DEMQOL [16]. Expressing this change as an effect size gives 5.1/12 = 0.425.

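### The hub targets add up to 60-75 care homes, short of the 80 clusters behind the 960 recruited, 640 followed up and 90% power

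*Protocol article*

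**What the plan says.** Under Recruiting centres, the protocol article states: "Three recruiting hubs based in London and Buckinghamshire will each aim to recruit between 20 and 25 care homes". It describes no other source of homes.

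The number of clusters appears in three other places. The abstract's design paragraph says the trial "will take place for nine months across 80 care homes in the United Kingdom". Overall design describes a "cluster randomised controlled, two-arm trial to be run in up to 80 care homes". Number of participants and power of the study says: "Up to 80 suitable care homes, or units within larger homes, will be identified, recruited and randomised". That last section adds: "There will be no more than two units in any care home".

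The same section sets the number of residents: "the minimum target participant recruitment is 12 individuals with dementia per care home". It continues: "Therefore, the target minimum sample size is 960", with a suggested upper limit of about 1,280, which is 16 per home. It expects 8 of every 12 to be followed up, 640 in all, and applies a variance inflation factor of 1.35. It concludes that "the likely useable sample size of 640 participants will give 90% power using a significance level of 5" per cent, for a standardised effect of 0.3.

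**The concern.** All the totals in the sample size section are 80 times a per-home figure: 80 × 12 = 960, 80 × 16 = 1,280, 80 × 8 = 640. The hubs are asked for 60 to 75 homes. Even if each hub reaches the top of its range, the trial is five homes short of the number on which its power is quoted.

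In a cluster trial the number of clusters largely determines power, so this is more than a matter of wording. The Discussion presents the trial as the first adequately powered to show an effect on quality of life. If the homes recruited match the hub targets and each contributes what the calculation assumes, a null result would be credited with more power than the trial had. Near 60 homes, the chance of missing a true 0.3 SD effect would be about 19% instead of about 10%.

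**Working it through.** **Inputs.** From Recruiting centres: 3 hubs, 20 to 25 homes each. From Number of participants and power of the study: 80 clusters, 12 recruited and 8 followed up per home (two-thirds retention), suggested limit 16 recruited, intra-home correlation 0.05, effect 0.3 SD, significance level 5%. From Randomisation: 1:1 allocation. Assumed, because not stated: a two-sided test, equal cluster sizes, and no gain from baseline adjustment.

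**Hub total.** 3 × 20 = 60 and 3 × 25 = 75.

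**Formulas.** With k homes and m followed up per home:
- variance inflation factor VIF = 1 + (m − 1) × 0.05
- effective sample size = k × m / VIF
- non-centrality = 0.3 × √(effective sample size / 4)
- power = Φ(non-centrality − 1.96)

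**Reproducing the plan's figure.** VIF = 1 + 7 × 0.05 = 1.35. Effective size = 640 / 1.35 = 474.1. Non-centrality = 0.3 × √118.5 = 3.266. Power = Φ(1.306) = 90.4%, which agrees with the stated 90%. Homes needed for exactly 90% at m = 8: 1.35 × 4 × ((1.96 + 1.2816) / 0.3)² / 8 = 78.8, so 79.

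**At the hub targets, m = 8.**

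| Homes | Recruited at 12 | Followed up | Effective size | Power | Effect detectable with 90% power |
|---|---|---|---|---|---|
| 80 | 960 | 640 | 474.1 | 90.4% | 0.298 SD |
| 75 | 900 | 600 | 444.4 | 88.5% | 0.308 SD |
| 60 | 720 | 480 | 355.6 | 80.7% | 0.344 SD |

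A t reference distribution with k − 2 degrees of freedom gives 89.7%, 87.7% and 79.4%.

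**Allowing more residents per home, at two-thirds retention.**
- 75 homes, 13 recruited: 75 × 13 = 975 recruited, m = 8.67, 650 followed up. VIF = 1.383, effective size 469.9, non-centrality 3.25, power about 90%. The 960, the 640 and the 90% are all met.
- 75 homes, 16 recruited: m = 10.67, 800 followed up, VIF = 1.483, effective size 539.3, power 93.6%.
- 60 homes, 16 recruited: 60 × 16 = 960 recruited, 640 followed up, VIF = 1.483, effective size 431.5, power 87.6%. The totals match the plan, but the larger clusters raise the VIF and the power falls short.
- 60 homes, 90% power: needs m of about 12.2, so 12.2 × 1.5 = 18.3 recruited per home, above the suggested limit.

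**Sensitivity to the correlation.** At 0.03 and m = 8, power is 84.8% with 60 homes and 91.6% with 75.

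**The case against.** The strongest reply is that the minimum of 12 per home is not a fixed number. The plan collects data on all consented eligible residents and suggests up to 16 per home, so one more recruit in each of 75 homes restores both 640 and 90%. This stands, and it removes the problem at the top of the hub range. It does not do so at 60 homes, where 16 per home still leaves 87.6%. The quoted power itself assumes 8 followed up, not more.

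Second, 80 is worded as a ceiling in two of the three places, and the hub figures are aims. This softens the conflict. But the minimum of 960 is the per-home minimum multiplied by the full 80, so the power is quoted at the ceiling.

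Third, a cluster may be a unit within a larger home, at most two per home. Five homes with two units each would turn 75 homes into 80 clusters. The document does not say that this is intended, and other sections point the other way. The design section places all recruited residents of a home in one arm, the randomisation and home selection sections allocate homes, and the quantitative analysis has only two levels, home and resident.

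Fourth, the inputs are cautious. The article says correlations rarely exceed 0.05, and the analysis adjusts for baseline, which the calculation does not credit. A null result would also be read with its 95% confidence interval. These points limit the practical loss but do not make the home counts agree.

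**Conclusion.** The inconsistency is real. The hub targets of 60 to 75 homes do not reach the 80 clusters on which the 960, the 640 and the 90% rest. At 8 followed up per home they give 480 to 600 residents and about 81% to 88.5% power, unless more residents per home make up the difference.

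A reader might infer that the plan cannot deliver 640 residents or 90% power, or that the trial has only about 80% power. The document does not support either. The 12-to-16 range allows both targets to be met with 75 homes, and the lowest figure requires every hub to be at its lowest target and every home to be at minimum recruitment. The loss is under two percentage points at 75 homes and material only near 60.

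The figures rest on a two-sided 5% test, equal cluster sizes, correlation 0.05, two-thirds retention at every recruitment level, and no credit for baseline adjustment.

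**What to change.** Make the abstract, the sample size section and the section on recruiting centres agree, in one of two ways:
- state hub targets that sum to 80, about 27 each (80 / 3 = 26.7); or
- restate sample size and power for 60 to 75 homes, giving the recruited and followed-up residents per home that the figure assumes, for example 88.5% at 75 homes and 80.7% at 60 homes with 8 followed up in each.

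In either case, say whether two units in one home are randomised and analysed as separate clusters or as one, and use the same unit in the hub targets and in the power calculation.

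The second option is a wording change that needs no extra residents; its cost is a slightly less favourable stated power. The first keeps the 90% but asks the hubs for about 5 more homes than the top of their present range, or 20 more than the bottom.

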### Participant selection: inclusion, exclusion and withdrawal criteria

All residents who would be potentially eligible for evaluation will be identified by the care home staff.

Inclusion for evaluation:

• All individuals residing in participating care homes who meet diagnostic criteria for dementia and/or score ‘1’ or greater on the CDR [19].

Exclusion from evaluation:

• Any resident from whom consent or the advice of a consultee cannot be obtained.

Withdrawal criteria:

• Individual participants will be able to withdraw from the study evaluation at any time.

### Data management and analysis

#### Safety reports of serious adverse events (SAEs)

Reports of SAEs will be performed according to the National Research Ethics Service (NRES) and NHS guidelines for safety reporting for research other than Clinical Trial of Investigational Medicinal Products (CTIMP).

### Assessment and follow-up

Assessments will be made at pre-baseline to assess the suitability of the care homes for inclusion. This process will include assessments to identify the total number of participants likely to be eligible for screening. Participants will be screened and consent obtained prior to baselining and to the care homes being randomised. Follow-up assessments will be made at nine months after commencement of the intervention.

### Data management and analysis

It is planned that anonymous data and all appropriate documentation will be kept securely for a period of seven years following the completion of the trial, subject to discussion with relevant ethics committees.

### Quantitative data management

Administrative databases will be held at the study centre. All participants and care homes will be identified by a unique study number; this number will be used to tag all research data sent outside the study centre, for example to NWORTH CTU. Quantitative research data will be entered via a web interface to the MACRO™ research databases held at NWORTH. The research team in the study centre will conduct primary data management, and the secondary cleaning and preparation of the data for analysis will be conducted by NWORTH. Consideration will be given to the differential time between baseline assessments and the start of intervention, adjusting for the time differences to an analysis as necessary.

### Quantitative analysis

Outcome measures for the study will be assessed at baseline and at nine months. All the outcome measures collected will be described and reported using appropriate descriptive statistics and tabular and graphical techniques. Means with 95% confidence intervals will be quoted and a 5% significance level will be reported.

The Consolidated Standards of Reporting Trials (CONSORT) diagram information will be presented in order to identify any differential dropout between the arms of the trial.

The analysis of the quantitative outcomes will involve a multilevel analysis of covariance (ANCOVA). Logistic regression will be used to assess whether the missing status can be predicted from any of the factors and covariates measured at baseline. The variables which are identified to affect the missing status will be included in the analysis model [31]. The primary outcome measure (DEMQOL proxy) [22] and the secondary outcome measures will be analysed using the multilevel modelling approach to ANCOVA. The value at nine months will be the response. The baseline value will be the covariate. The key factor will be group (treatment or control). The multilevel nature of the design will be represented by two levels: care home and individual residents in the care home.

Other covariates, whether at the care home level (for example, number of residents) or the resident level (age, gender) will be investigated to see whether they have an effect on the response measure and included as necessary.

A full statistical analysis plan will be developed through the course of the study.

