### Randomisation

Care homes will be allocated to either receive the optimised WHELD intervention or TAU using secure web access to the remote randomisation centre at North Wales Organisation for Randomised Trials in Health Clinical Trial Unit (NWORTH CTU), at Bangor University. This system will be set up, maintained and monitored independently of the trial statistician or other trial staff. The randomisation will be performed by dynamic allocation [17] to protect against subversion while ensuring that the trial maintains good balance to the allocation ratio of 1:1 both within each stratification variable and across the trial. Care homes will be stratified by region and size. The system has been coded and validated in the R statistical package.

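### Homes are allocated by region and size, but neither is a fixed term in the primary model, and home size enters only through a screen on the nine-month response that has no stated criterion

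*Protocol article*

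**What the plan says.** On allocation, the Randomisation section of the protocol article states: "Care homes will be stratified by region and size". The method is dynamic allocation, aimed at a 1:1 ratio within each stratification variable and across the trial.

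On analysis, the Quantitative analysis section specifies a multilevel ANCOVA for the primary outcome (DEMQOL-Proxy) and for the secondary outcomes. The nine-month value is the response, the baseline value is the covariate, arm is the key factor, and the levels are care home and resident. These are the only terms fixed in advance.

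Other covariates, with number of residents as the home-level example and age and gender as the resident-level examples, "will be investigated to see whether they have an effect on the response measure and included as necessary". Region does not appear in the analysis text.

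A separate step uses logistic regression to find baseline predictors of missing status: "The variables which are identified to affect the missing status will be included in the analysis model". A full statistical analysis plan is deferred to the course of the study.

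**The concern.** Variables used to balance an allocation belong in the analysis, whether or not they look significant. Balancing on a prognostic factor reduces the true variability of the treatment contrast. A model without that factor leaves its variance in the between-home error, so the reported standard error does not reflect the gain. Confidence intervals are then too wide and the test rejects too rarely under the null.

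Here home size must earn its place by its observed effect on the response. Region could enter only by the same route. Because no threshold, candidate list or order of testing is given, two analysts following the text could arrive at different primary models and different primary estimates. The same approach serves the secondary outcomes, so the covariate set could also differ from outcome to outcome.

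**Working it through.** **Inputs from the section on number of participants and power.** The plan has "Up to 80 suitable care homes, or units within larger homes, will be identified, recruited and randomised". It expects 8 residents per home at nine months, 640 in all, and takes an ICC of 0.05 ("intra-home correlation coefficients rarely exceed 0.05"). The target is "a standardised effect size of 0.3 SDs" at the 5% level. Sidedness is not stated, so two-sided is assumed. Allocation is 1:1, so 40 homes per arm.

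**Assumption.** The documents do not give the share r of between-home variance that region and size explain. A range of 20-60% is shown, with 0 for reference.

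**Step 1: the plan's own figure.** The plan says that "the likely useable sample size of 640 participants will give 90% power". The variance inflation factor is 1 + 7 × 0.05 = 1.35, and the effective sample is 640/1.35 = 474, or 237 per arm. The standard error is √(2/237) = 0.0919, and power is Φ(0.3/0.0919 − 1.96) = 90.4%. With a t distribution on 80 − 2 = 78 degrees of freedom it is 89.7%. The stated 90% reproduces, and the calculation takes no credit for stratification or baseline adjustment.

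**Step 2: full omission of both factors, ICC 0.05.** The variance of a home mean is

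- as seen by the model without the strata: v0 = 0.05 + 0.95/8 = 0.16875
- true for the balanced contrast, and as seen by the model with the strata: v1 = 0.05(1 − r) + 0.95/8

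The standard errors are SE0 = √(2·v0/40) and SE1 = √(2·v1/40). With the strata omitted, the actual type I error is 2[1 − Φ(1.96·SE0/SE1)] and power is Φ((0.3 − 1.96·SE0)/SE1). With the strata fitted, power is Φ(0.3/SE1 − 1.96).

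| r | v1 | SE0/SE1 | Type I error, omitted | Power, omitted | Power, fitted |
|---|---|---|---|---|---|
| 0 | 0.16875 | 1.000 | 5.0% | 90.4% | 90.4% |
| 0.2 | 0.15875 | 1.031 | 4.3% | 91.1% | 92.0% |
| 0.4 | 0.14875 | 1.065 | 3.7% | 91.8% | 93.6% |
| 0.6 | 0.13875 | 1.103 | 3.1% | 92.5% | 95.0% |

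**Step 3: a lower ICC.** With an assumed ICC of 0.02, v0 = 0.02 + 0.98/8 = 0.1425. Over the same range of r, the standard error is overstated by 1.4-4.5% and the power difference is 0.3-0.8 points, with power about 95% either way.

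**Step 4: selection in place of omission.** Home means were simulated for 80 homes with an assumed three regions and two size groups, stratified 1:1, and with the explained variance split equally between region and size (10,000 null and 6,000 alternative runs per setting). The plan gives no selection rule, so p < 0.05 for size was assumed.

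| Share explained | Quantity | Both omitted | Size added if p < 0.05 | Both fixed |
|---|---|---|---|---|
| 50% | Power | 91.1% | 92.3% | 93.4% |
| 50% | Type I error | 3.6% | 4.3% | 5.3% |
| 75% | Power | 92.0% | 93.8% | 95.1% |
| 75% | Type I error | 2.5% | 3.6% | 4.9% |

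Over shares of 0-75%, selecting size gave a type I error of 3.6-5.1%. Taking the smallest p-value of three models (neither factor, size only, both) gave 4.9-5.4%.

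**The case against.** The list of further covariates is open, and region is a home-level variable, so a reader who infers that the plan excludes region goes beyond the text. A condensed article may also leave the full covariate list to the analysis plan. That part of the objection stands. What remains is that the article does state a rule, namely inspecting the effect on the response and then deciding, and that rule covers home size explicitly. Deferring the full plan does not withdraw it.

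The figures for full omission also price the worst case. A factor that explains much variance is the one most likely to be selected, and in the simulation selecting size alone recovered about half of the lost power. The assumed ICC of 0.05 is near the top of what the protocol expects, and the baseline covariate may already absorb some stable differences between homes. These points stand and reduce the size of the effect.

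A reader might further infer that the trial is underpowered or that the 5% level is breached. Neither is supported. Every power figure in Step 2 is above 90%, so what is forgone is precision that the sample size never claimed. The simulation shows no material inflation, although it covers only a few models while the plan's list of candidates is open.

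Finally, the step for predictors of missingness might be read as more outcome-based selection. It selects on missing status and not on outcome values. With 8 of 12 residents expected at follow-up, so that one third are lost, it has a legitimate purpose in making a missing-at-random assumption more plausible.

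**Conclusion.** The point holds as a weakness in how the primary model is specified. Neither allocation factor is a fixed term, and home size is left to an outcome-based screen without a criterion, so the primary estimate cannot be written down in advance.

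The statistical cost is modest and conditional. At ICC 0.05, with 20-60% of the between-home variance explained and both factors left out, it is a standard error about 3-10% too large, a type I error of about 4.3-3.1% and about 1-2.5 points of attainable power. It is smaller at a lower ICC or if size is selected, and nil if the factors do not predict the outcome. The share explained is an assumption throughout. The main reason to change the text is that the primary analysis should not rest on the analyst's discretion once outcomes are known. The change is worth making because it costs almost nothing, and not because validity or planned power is at risk.

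**What to change.** In the Quantitative analysis section, state that region and home size, in the form used for the allocation, enter the primary model as fixed terms whatever their significance, alongside arm, the baseline value and the home level. Say that the same holds for the secondary-outcome models that use this approach.

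Replace the clause "will be investigated to see whether they have an effect on the response measure and included as necessary" with a list of any further covariates, named before outcome data are seen. Whether age and gender are on that list is for the trial team to decide, provided that it is settled in advance.

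The step that adds predictors of missingness can stay as written.

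The cost is a paragraph of wording and a few of about 78 home-level degrees of freedom. With three regions and two size groups, for example, it would be 2 + 1 = 3. No change to the sample size follows.
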